In Tanzania PZQ at 40mg/kg body weight as a single dose has been tested against infections by *S haematobium* (McMahon & Kolstrup, 1979) and *S mansoni* (Rugemalila et al., 1984). McMahon & Kolstrup (1979) recorded high cure rates of 83%, 76% and 71% against *S haematobium* at 1- month, 2- months and 6- months, respectively. In *S mansoni*, however, Rugemalila et al. (1984) observed lower cure rates of 35%, 56% and 63% at 1-month, 2- months and 6- months, respectively.

The unusually low cure rates reported by Stelma et al. (1995) in Senegal, while working in very intense focus of *S. mansoni*, has raised much concern about the emergency of resistance or tolerance of schistosomes to PZQ. So in order to circumvent this problem, several strategies to reduce the rate of schistosome species developing resistance against PZQ and to optimize the use of PZQ in schistosomiasis control has been suggested. In the present study, the suggested option to be explored is to increase the dose regimens of PZQ up to 60mg/kg body weight.

Stelma et al. (1997) increased the dose of PZQ from standard dosage of 40mg/kg to 60mg/kg and showed to have no significant improvement in efficacy. Van Lieshutt et al. (1994), however, showed that the opposite was true. This controversy requires to be urgently resolved by collecting data on the safety, efficacy and effectiveness of increased doses of PZQ in different epidemiological setting where schistosomiasis is highly endemic.

Children are especially vulnerable to schistosomiasis, and infected school-age children are often physically and intellectually compromised by concurrent anemia, attention deficits, learning disabilities, school absenteeism and higher dropout rates (Guyatt et al., 2001; WHO, 2002). Schistosomiasis Control Programs target school-aged children, aiming for clinical cure and morbidity reduction. Many previous trials were done with children and adolescents to test the efficacy of praziquantel alone or in combination with other drugs (Jaoko et al., 1996; Guisse et al., 1997; Olds et al., 1999; Urtzinger et al., 2000; de Clercq et al., 2002). Since praziquantel is a safe and well known drug (as described above) and the improvement of treatment should be achieved for those who need the most, children and adolescents will be the chosen study population for this trial.

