## **3. EXPERIMENTAL DESIGN AND METHODS**

The trial described below will be conducted in compliance with the protocol, Good Clinical Practice and applicable regulatory requirements.

3.1. *Study site.* The study is to be done in Mwanza Region, Tanzania, where both *S. mansoni* and *S. haematobium* are highly endemic particularly in Magu and Misungwi districts. In a recent survey of schoolchildren by [name], *et al* (1999) in the area the prevalence of urinary schistosomiasis was found to be 56.5% (range 13.6-87.7%) and 10.9 % (range 0.0-64.4%) for intestinal schistosomiasis. *S. mansoni* is more prevalent along the Lake Victoria shore, while *S. haematobium* is more prevalent in the hinterland, away from the lakeshore. In this area mixed *S. haematobium/ S. mansoni* infections have a low prevalence of 4.0 % (range 0.0 – 21.0 %). The study will be done in schools reported by [name] *et al.* (1999) to have high prevalence of *S. mansoni*, i.e., Mayega 64.7%, Kigangama 53.3%, Lutale 49.5%, Kongolo 41.7%, Chumve 41.5%, Kabita 39.8%, Ihale 38.0% and Ilumwa 34.4%. Also schools located in the same area as the high prevalence schools may be considered for baseline screening. [name] (1988) have shown that peak transmission of *S. haematobium* in the area occurs during the short dry period, sometime in February/March so that most of the infections in the community would be detected in April/May. Magendantz (1972) showed that the transmission of *S. mansoni* occurs mainly in Lake Victoria throughout the year.

3.2. *Study design.* The proposed study is a double-blind, randomized controlled trial to determine if higher doses of praziquantel (PZQ 60mg/kg) will improve treatment efficacy of *S. mansoni* with an adequate safety profile, in comparison with standard regimen of PZQ 40mg/kg. The trial is to be conducted with schoolchildren aged between 10 to 19 years old. This age group is chosen because it is

school age children who are heavily infected by schistosomes, therefore, it is the group in which the new increased dosage of PZQ is anticipated to be used. The potential beneficiary of increased efficacy of PZQ is school-age children and, therefore, it would be prudent to determine the safety profile of the new dosage regimen in the same age group.

The following are the study endpoints:

- Primary endpoint:  
Cure rate at 21 days after treatment for the PZQ 60mg/Kg and PZQ 40mg/Kg groups.
- Secondary endpoints:

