#### D21 (means 21 days after treatment +/- 2 days)

The physician in the research team will assess schoolchildren treated on D0 for adverse events using a questionnaire. In addition, Hb will be determined in all schoolchildren in the trial. Stool samples will be collected on two separate days and each day duplicate Kato Katz slides will be made for quantitative examination of *S mansoni* ova. This will allow cure rate and egg reduction rate at D21 to be calculated.

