#### 7.2. Methods for assessing efficacy:

- Cure rate will be estimated as the proportion of subjects with negative result at 21 days after treatment.
- Egg reduction rate at 21 days after treatment will be estimated through the following formula:  
 $[1 - (\text{epg2} / \text{epg1}) \times 100]$  where epg1 and epg2 are the geometric mean of  $\log_{10}$  transformed (x+1) numbers of eggs per gram of faeces at the screening survey and the 21st day post-treatment survey.

The same calculations of cure rate and egg reduction rate will be estimated for the 6M and 12M follow-up in order to estimate reinfection rates.

7.3. Analysis: The cure rate and egg reduction rate will be compared between the 2 treatment regimens, PZQ 40mg/Kg and 60mg/Kg.

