## **10. DATA PROCESSING AND ANALYSIS**

The data will be double entered into a computer using dBase programme by two different data entry clerks and the entered data will then be verified and cleaned before being subjected to analysis using STATA.

10.1. Analysis of data: Chi- square or Fisher's exact test will be used for comparison of proportions (ex. cure rate & egg reduction rate, frequency of AEs and severity of AEs) and Student's t test for comparison of means (geometric mean egg output, variation of Hb level and weight) in the two treatment groups (PZQ 40mg/kg and 60mg/kg).

10.2. Sample size:

Assuming the cure rate of a standard dosage (40mg) of Praziquantel is 60% and increasing the dosage to 60mg would improve cure rate to *at least* 80%, a sample size of 91 infected schoolchildren per study group will be needed. This sample size will give a study power of 80% at 5% significance level. Considering a drop out of about 30% due to loss to follow-up or medical grounds, 118 study subjects will be needed for each study group making a total of 236 schoolchildren.

10.3. Quality Control:

During laboratory examination of stool and urine specimens, a 10% sample of specimens will be re-examined by an independent technician (one who is not part of the research team) every day and results compared to see the degree of agreement.

10.3.1. For Kato-Katz examinations:

10% of the slides read by each microscopist will be randomly selected and re-examined by an experienced microscopist designated by the PI.

*For cure rate* (agreement between positive/negative slides) the maximum discordance rate acceptable will be 5%. Above 5% all slides will have to be read by the experienced microscopist.

*For infection intensity*, levels of infection will be defined as:

| Number of eggs/slide | Approximate egg count/g of stools |
|----------------------|-----------------------------------|
| 1-4                  | ~ 1-100                           |
| 5-12                 | ~ 100-300                         |
| 13-25                | ~ 300-600                         |
| 26-41                | ~ 600-1.000                       |
| >41                  | ~ 1.000                           |

Disagreement will be defined when the 2 readings result in different levels of infection, according to this classification. The maximum level of disagreement accepted will be 5%.

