## **12. CRITICAL ASSESSMENT AND POSSIBLE LIMITATION OF APPROACH IN RELATION TO PROJECT OBJECTIVES**

12.1. Missing of a single schistosome egg during microscopy in light infections may cause bias in determination of cure rate and egg reduction rate (efficacy) of the investigational product. To minimise bias only subjects with high egg count are included in the trial (see inclusion criteria)

12.2. Praziquantel does not affect immature stages of schistosomes. In order to avoid eggs from immature stages that are not affected by PZQ at the time of treatment, the end point in determination of efficacy is optimised at day 21.

## APPENDIX 1

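### The 60% control cure rate in section 10.2 has no source or time point and is 25 points above the cited rate nearest to day 21; section 7.2 cannot get reinfection from overall 6M and 12M cure rates

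*Protocol*

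**What the plan says.** The primary endpoint in Protocol section 3.2 is "Cure rate at 21 days after treatment for the PZQ 60mg/Kg and PZQ 40mg/Kg groups". The visit window is ±2 days. Section 12.2 says that "the end point in determination of efficacy is optimised at day 21", and the reason it gives is that praziquantel does not act on immature worms.

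Section 10.2 sizes the trial on this basis: "Assuming the cure rate of a standard dosage (40mg) of Praziquantel is 60" per cent, and "increasing the dosage to 60mg would improve cure rate to" at least 80%. This gives 91 per group for 80% power at the 5% level, raised to 118 per group for dropout. No source or time after treatment is attached to the 60%.

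The Introduction describes Tanzanian trials of the same single 40 mg/kg dose as the control arm ("In Tanzania PZQ at 40mg/kg body weight as a single dose has been tested against infections by" both species). For *S. mansoni*, the local trial "observed lower cure rates of 35%, 56% and 63% at 1-month, 2- months and 6- months, respectively". The Introduction also mentions low cure rates in Senegal and two conflicting comparisons of dose, but gives no figures for them.

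Section 7.2 says that the same cure and egg-reduction calculations will be "estimated for the 6M and 12M follow-up in order to estimate reinfection rates".

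**The concern.** A planning rate for a binary endpoint has to refer to the time at which the endpoint is read. In the one numerical *S. mansoni* series the protocol cites, the proportion counted as cured differs by 28 points between 1 and 6 months (63 − 35). That is more than the 20-point effect the trial is sized to detect. Day 21 is earlier than every time point in the series, and 60% falls between its 2- and 6-month values. Section 12.2 explains why day 21 was chosen, but not why 60% should hold then. If control cure at day 21 is nearer 35%, the stated 80% power does not describe the comparison that will be made.

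The second issue is the use of the later visits. A child who is egg-positive at 6 months may never have been cleared or may have been cleared and reinfected. A child who is negative at 6 months may have cleared after day 21. An overall 6M or 12M cure rate does not separate these groups, so it cannot by itself give a reinfection rate.

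**Working it through.** **Inputs.** From section 10.2: control 60%, comparator 80%, power 80%, 5% level (two-sided assumed, since sidedness is not stated), 91 per arm. From the Introduction: 35%, 56% and 63% at 1, 2 and 6 months on 40 mg/kg. From section 3.3: 1:1 allocation.

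**Step 1: reproduce the plan's figure.** With p̄ the mean of p₁ and p₂, and d their difference:

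n = [1.960·√(2p̄(1−p̄)) + 0.842·√(p₁(1−p₁) + p₂(1−p₂))]² / d²

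For 60% v 80%: [1.960·√0.42 + 0.842·√0.40]² / 0.04 = 81.2.

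Continuity correction: (n/4)·[1 + √(1 + 4/(n·d))]² = (81.2/4)·[1 + √1.246]² = 90.9, which rounds up to 91. The stated figure is reproduced. The arithmetic is sound and the question is the input.

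**Step 2: compare the input with the cited rates.** 60 − 35 = 25 points above the 1-month rate; 60 − 56 = 4 points above the 2-month rate; 63 − 60 = 3 points below the 6-month rate.

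**Step 3: put 35% in for the control rate.** The plan's 60% v 80% can be carried over on three scales:

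- Same difference: 35 + 20 = 55%.
- Same risk ratio: 0.80/0.60 = 1.33, so 0.35 × 1.33 = 46.7%.
- Same odds ratio: (0.80/0.20)/(0.60/0.40) = 2.67. The odds at 35% are 0.35/0.65 = 0.538, and 0.538 × 2.67 = 1.436, so the rate is 1.436/2.436 = 58.9%.

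The required n uses the corrected formula of step 1. For 35% v 55%: [1.960·√0.495 + 0.842·√0.475]² / 0.04 = 95.9 before correction and 105.7 after. Exact power sums the binomial probabilities of all outcome pairs with 91 per arm for which the chi-square test rejects.

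| Contrast | Scale kept | n per arm, corrected | Exact power at 91, uncorrected (corrected) |
|---|---|---|---|
| 60% v 80% | plan | 91 | 85% (80%) |
| 35% v 55% | difference | 106 | 77% (72%) |
| 35% v 46.7% | risk ratio | 295 | 36% (31%) |
| 35% v 58.9% | odds ratio | 76 | 90% (87%) |

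**Step 4: section 7.2.** Suppose day-21 cure is the assumed 60%, no positive child clears later and nobody is reinfected. Then 100 − 60 = 40% are positive at 6 months, and none of that is reinfection. Late clearance would lower the 40% and reinfection would raise it, so one overall rate cannot separate the two. Restricting to children negative at day 21 removes those still positive then from the reinfection estimate.

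**The case against.** The strongest reply is that one older series is a thin basis for challenging the assumption. The protocol does not say that 60% came from that trial, and 60% is neither 56% nor 63%. A reader might infer that a 2- to 6-month rate was transplanted to day 21, but the text shows only that the rate is unsourced and far from the nearest cited figure. One month is also not day 21. Nor do the documents show whether the cited trial resembles this one in slide number, age or the minimum of 100 eggs per gram. All of this stands, and it is why the request is to justify the rate rather than replace it with 35%.

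A reader might also infer that many day-21-positive children would become negative later. Three group percentages without denominators, losses or retreatment details do not show that. They may not even describe the same children at each visit.

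The power effect can be contested too. With the odds ratio kept, power rises. The 30% loss allowance is not tied to a visit, and 118 per arm are enrolled. If only 10% were lost by day 21 (an assumption; 118 × 0.90 ≈ 106), 35% v 55% would have 83% (79% corrected) power. If the full 30% were lost (118 × 0.70 ≈ 82), it would have 74% (68%), but much of that shortfall comes from the dropout inflation, a separate matter.

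Finally, cure at 6 months is already measured, section 7.3 already compares cure between arms, and further tables could sit in an analysis plan. That is fair for table layout. It does not rescue the stated purpose in section 7.2, which assigns the overall later rates to reinfection.

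**Conclusion.** The point holds in a limited form. Section 10.2 fixes a control rate for a day-21 endpoint without source or time point, 25 points above the nearest rate the protocol cites. The 80% power is correct arithmetic for 60% v 80%, but the protocol's own evidence does not support it for day 21.

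It does not follow that the trial is underpowered. At a 35% control rate and 91 evaluable per arm, uncorrected power runs from 36% to 90% depending on whether the risk ratio, the difference or the odds ratio is kept, and the protocol does not say which it means. These figures rest on a two-sided 5% test and on taking the 1-month rate as a low case for day 21.

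Section 7.2 as written cannot deliver reinfection rates from the overall 6M and 12M cure rates, whatever the control rate proves to be. A reader might go further and require a null result at day 21 to be read jointly with later clearance. The documents do not support that: the primary endpoint is single and clear, and children positive at day 21 are a subset defined after randomisation.

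**What to change.** **Section 10.2.** State the control cure rate expected at day 21 and its source. Say whether the target gain is a difference, a risk ratio or an odds ratio. Restate power at the planned size for control rates from 35% (the cited 1-month figure, as the low case) to 60%. No patients need be added.

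**Section 7.2.** Estimate reinfection at 6M and 12M among children who were egg-negative at day 21. Tabulate by arm, descriptively, the day-21-positive children who are negative at 6M. Note beside the table that missed eggs in light infections (section 12.1) and reinfection under year-round transmission (section 3.1) also affect it, so it does not isolate late clearance.

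**Cost.** Wording in two sections and one table from stool samples already scheduled, with no change to endpoint, visits, treatment or sample size. The stated power may become less favourable.

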### **5. TREATMENT OF SUBJECTS:**

Those schoolchildren who fulfilled inclusion criteria will be recruited for the trial. A total of 236 schoolchildren (see sample size calculation on section 10.2) with *S. mansoni* who fulfilled the inclusion/exclusion criteria would be randomly assigned to two groups of 118 each. One group will be given a single dose of PZQ 40 mg/kg and the other a single dose of PZQ 60mg/kg body weight. Table 2 below illustrates the treatment groups.

Table 2. Study groups for and *S. mansoni* treatment.

| Dosage of PZQ/kg body weight | S. mansoni subjects (N) |
|------------------------------|--------------------------------|
| 40 (single dose) – Control   | 118                            |
| 60 (single dose)             | 118                            |

Praziquantel is provided in tablets of 600mg with 3 scores, which may be divided in 4 segments of 150 mg each. The amount of drug to be given can be adjusted to the patient's bodyweight by breaking the tablets in 4 segments. A reference table for the number of tablets to be given for each participant according to treatment regimen and body weight is presented in Appendix 2.

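### The drop-out allowance in Protocol section 10.2 multiplies 91 by 1.3 instead of dividing by 0.7, so 118 per arm covers about 23% loss, not the stated 30%

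*Protocol*

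**What the plan says.** Section 10.2 assumes cure of 60% on 40 mg/kg and at least 80% on 60 mg/kg. It concludes that "a sample size of 91 infected schoolchildren per study group will be needed" and adds: "This sample size will give a study power of 80% at 5% significance level". The allowance for loss follows: "Considering a drop out of about 30% due to loss to follow-up or medical grounds, 118 study subjects will be needed" in each group, 236 in total. Section 5 carries the figure into the treatment plan, where the children "would be randomly assigned to two groups of 118 each".

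Four other statements matter here:

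- Section 3.2 makes cure at 21 days the primary endpoint and sets follow-up at 12 months.
- Section 3.2 also expects about 240 eligible children from 800 screened.
- Section 4.3 says that withdrawn participants are not replaced.
- Section 10.1 offers a chi-square or Fisher's exact test for all comparisons of proportions. It does not say which applies to the cure rate, or whether the chi-square is continuity-corrected.

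**The concern.** A loss allowance has to be set so that the children who remain after the loss equal the number required, so the required number is divided by the retained fraction. Adding 30% to the required number does something else, because the 30% is then lost from the larger total. The protocol's three figures (91 needed, about 30% lost, 118 enrolled) therefore do not agree with each other. With no replacement of withdrawals, nothing later in the protocol makes up the difference.

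What is at stake is the power for the primary endpoint. The protocol presents 118 per arm as enough to keep the 80% power attached to 91 after a 30% loss. Whether it is enough depends on the test used and on the loss by day 21.

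**Working it through.** **Inputs.** All are from section 10.2 unless noted: cure 0.60 and 0.80; power 80%; significance level 5%; 91 per arm before loss; loss about 30%; 118 per arm after the allowance; 1:1 allocation (section 3.3). The protocol does not say whether the test is one- or two-sided. Two-sided is assumed because it reproduces the 91.

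**Step 1: reproduce the 91.** With pooled rate 0.70 and difference 0.20, the uncorrected two-sided formula is

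n = [1.960 × √(2 × 0.70 × 0.30) + 0.842 × √(0.60 × 0.40 + 0.80 × 0.20)]² / 0.20² = 81.2, so 82.

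The continuity-corrected number is

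n′ = (n/4) × [1 + √(1 + 4/(n × 0.20))]² = (81.2/4) × [1 + √(1 + 4/16.24)]² = 90.9, so 91.

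Other common variants at 80% power do not give 91: unpooled 79, arcsine 81, one-sided 64 (uncorrected) or 74 (corrected). The 91 therefore matches a two-sided continuity-corrected test.

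**Step 2: reproduce the 118.** 91 × 1.3 = 118.3.

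**Step 3: check the 118 against the stated loss.**

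- Remaining after 30% loss: 118 × 0.70 = 82.6, so 82 to 83 per arm, which is 8 to 9 short of 91.
- Loss that 118 can absorb while keeping 91: 1 − 91/118 = 22.9%.
- Enrolment that would keep 91 at 30% loss: 91/0.70 = 130 per arm, 260 in total.

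**Step 4: power at the reduced number.** Exact power for 60% against 80%, two-sided 5%, by full enumeration of both binomial distributions:

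| Evaluable per arm | Fisher's exact | Continuity-corrected chi-square | Uncorrected Pearson chi-square |
|---|---|---|---|
| 82 | 75.9% | 75.9% | 80.7% |
| 83 | 76.7% | 76.7% | 81.4% |
| 91 | 80.8% | 80.2% | 84.7% |

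The normal approximation at 82 agrees: 75.2% with the continuity correction and 80.4% without it. Rounding 82.6 down or up does not change the conclusion.

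**The case against.** The strongest reply has three parts.

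**The power sentence.** It is attached to 91, and at 91 it holds for every candidate test. At 82 the uncorrected chi-square still reaches 80%. This stands, and it limits the finding to a wrong allowance with a conditional loss of power. A reader might infer that the trial is underpowered, or that it must enrol 130 per arm. The documents do not support either. The 130 is needed only if 91 must survive a 30% loss, and the uncorrected test does not need 91. A total of 260 would also exceed the roughly 240 eligible children expected.

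**The choice of test.** Fisher's test may be meant only for sparse tables such as adverse events. For cure at 82 per arm the smallest expected cell is about 0.30 × 82 = 24.6, so a chi-square would be the usual choice. That is plausible, and the correction could be settled in an analysis plan not shown here. But the protocol states no such rule, and its own 91 follows from a corrected test.

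**The timing of the loss.** The 30% has no time point, and follow-up runs for 12 months. Loss by day 21 could be well below 30%; at 22.9% or less, 91 remain. This stands as well, so the power figures must be given as conditional. It does not repair the arithmetic, because the protocol applies the 30% without qualification and gives no separate day-21 rate.

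A further inference is tempting. The Introduction cites an earlier Tanzanian trial at 40 mg/kg that "observed lower cure rates of 35%, 56% and 63% at 1-month, 2- months and 6- months", so a reader might call the 60% planning rate wrong for a day-21 endpoint. The documents do not show that. The 60% is a planning assumption with no stated source, and the 35% is a single earlier result at one month. The effect on power also has no fixed direction. At 82 per arm with 35% control cure, power is 68% (Fisher) or 74% (Pearson) for the same 20-point gain, but 84% or 87% for the same odds ratio (2.67). It is not part of this finding.

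**Conclusion.** The allowance is miscalculated: 118 per arm covers 22.9% loss, not 30%, and at 30% about 82 to 83 children per arm remain instead of 91. If all of that loss falls before day 21, power under the protocol's own rates is about 76% with Fisher's exact or a continuity-corrected chi-square, 4 to 5 points below its level at 91. With the uncorrected Pearson chi-square it is about 81%, and the 80% target is met.

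This rests on the stated 60% and 80% cure rates, a two-sided 5% test, equal loss in both arms, and the whole 30% being lost by day 21. The arithmetic error does not depend on the last two assumptions; the power figures do. Severity is moderate: a planning figure is wrong and should be corrected, but the design can stand.

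**What to change.** Change sections 10.1 and 10.2 only.

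- In 10.2, say that 118 per arm keeps 91 evaluable at a loss of up to about 23%, and leaves about 82 at a loss of 30%.
- In 10.1, name the uncorrected Pearson chi-square as the primary test for day-21 cure. In 10.2, restate the requirement on that basis: about 82 evaluable per arm for 80% power. The 91 should then no longer stand as the requirement, since it belongs to the corrected test.
- Alternatively, keep Fisher's exact or the corrected chi-square, leave 91 as the requirement, and state that power is about 76% if 30% are lost by day 21.

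The test should be fixed before outcome data are seen. The cost is a few sentences and, under the alternative, a less favourable power figure. Enrolment stays at 118 per arm and 236 in total.
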